## Abstract

**Background:**

Work stress has a detrimental impact on individual health and corporate efficiency and productivity. Mindfulness reduces workers’ stress and burnout and increases work engagement and performance. Smartphone-based interventions could be an alternative to provide customized training without geographical or economic constraints. This study aims to investigate whether mobile mindfulness training (MMT) improves office workers’ stress, burnout, and work engagement.

**Methods:**

This study is a two-arm randomized controlled trial. In total, 114 office workers will be randomly assigned to one of two groups: an experimental group and a control group. The experimental group will undergo MMT, following both daily and event guidelines, for the first 4 weeks. In contrast, the control group will not receive any intervention for the first 4 weeks. During the next 4 weeks, the control group will undergo MMT for ethical reasons. Assessments will be conducted at baseline, post-intervention (fourth week), and follow-up (eighth week). The outcomes are burnout, work engagement, perceived stress, mindfulness, and vitality.

**Discussion:**

This study will serve as a basis for evaluating the effectiveness of MMT on stress, burnout, and work engagement of office workers.

**Ethics and dissemination:**

This study was approved by the Institutional Review Board of Kyung-Hee University [KHSIRB-24-063(RA)]. The results will be disseminated through peer-reviewed publications.

**Clinical trial registration:**

Identifier [KCT0009458]. https://cris.nih.go.kr/cris/search/detailSearch.do?seq=26951&status=5&seq_group=26951&search_page=M

## Introduction

1

Work stress refers to a phenomenon in which personal factors and the workplace environment interact to negatively affect workers’ physical and psychological functions (1). Previous studies have shown that chronic stress at work can lead to physical illness and psychological disorders (2, 3). Work stress has a negative impact not only on an individual’s health but also on their attitude and performance toward their job. Work engagement refers to a state in which they highly identify with their job and are highly physically, cognitively, and emotionally involved in their job (4). Burnout, the opposite state of work engagement, appears as a response to chronic emotional and interpersonal stressors at work and results in exhaustion, cynicism, and lack of efficacy (5). In this way, chronic work stress could cause negative perceptions of the job and further worsen job performance. Indeed, previous studies have shown that excessive work-related stress reduces personal health and work motivation, increases mistakes and accidents, and ultimately reduces organizational efficiency and productivity (6, 7). According to other studies, work stress causes general health problems, increases burnout, and reduces job satisfaction and work engagement (8–10). For this reason, interest in methods for managing work stress is increasing. Common interventions for managing workers’ stress include mind–body interventions such as mindfulness and relaxation techniques (11).

Recently, various mobile healthcare applications have been developed for mental health management (12). Mobile-based interventions can deliver high-quality education without geographical and economic constraints and can provide customized education suitable for individuals (13). Furthermore, because these interventions are easy to standardize, they may be as effective in improving health outcomes as well-designed offline education (13). According to previous studies, mobile healthcare applications can reduce psychological symptoms, prevent disease, and improve wellbeing (14–16).

Mindfulness is a unique attentional ability developed through meditation practice, characterized by present-moment focus and nonjudgmental attitude. Mindfulness training is used to alleviate emotional problems and improve the quality of life in a variety of clinical groups. Previous studies have shown that mindfulness reduces stress, depression, and anxiety, and improves wellbeing (17–22). Furthermore, mindfulness training can improve workers’ mental health and job performance. According to previous studies, mindfulness reduces workers’ stress and burnout (23–26) and improves work engagement and job performance (27–29).

Because of these benefits, mindfulness has recently become a core component of several smartphone-based healthcare applications, such as Headspace and Calm. Previous studies have shown that mobile mindfulness training (MMT) reduces users’ stress, depression, and anxiety, and improves their quality of life (16, 30–33). However, most studies on the effects of mobile mindfulness training have been conducted on students or the general public, with relatively few studies targeting workers (16). Moreover, according to previous research (34), more than half of digital mindfulness-based intervention studies have been conducted with healthcare workers, while less than one-fifth of the studies have been conducted with office workers. Therefore, this study will investigate the effects of MMT on office workers’ stress, burnout, and work engagement.

This study aims to verify the effectiveness of MMT on the mental health of office workers and explore its mechanisms. The primary objective of this study is to investigate whether a four-week MMT improves office workers’ mental health, stress, burnout, and work engagement. The results of this study are predicted as follows: (i) The experimental group will exhibit reduced burnout compared to the control group after 4 weeks. (ii) The experimental group will exhibit enhanced work engagement compared to the control group after 4 weeks. (iii) The experimental group will exhibit lower perceived stress compared to the control group after 4 weeks. (iv) The experimental group will exhibit increased mindfulness compared to the control group after 4 weeks. (v) The experimental group will exhibit superior subjective vitality compared to the control group after 4 weeks.

The secondary objective of this study is to perform a follow-up examination to assess the effect of MMT on the mental health, stress, burnout, and work engagement of employees over a longer period. The results of this study are predicted as follows: (i) Burnout at follow-up will be lower than that at baseline in the experimental group. (ii) Work engagement at follow-up will be higher than that at baseline in the experimental group. (iii) Perceived stress at follow-up will be lower than that at baseline in the experimental group. (iv) Mindfulness at follow-up will be higher than that at baseline in the experimental group. (v) Subjective vitality at follow-up will be higher than that at baseline in the experimental group.

The third objective of this study is to examine differences in the effectiveness of MMT depending on the amount of application usage. The results of this study are predicted as follows: (i) The high-usage subgroup will exhibit a greater reduction in burnout compared to the low-usage subgroup after MMT. (ii) The high-usage subgroup will exhibit a greater increase in work engagement compared to the low-usage subgroup after MMT. (iii) The high-usage subgroup will exhibit a greater reduction in perceived stress compared to the low-usage subgroup after MMT. (iv) The high-usage subgroup will exhibit a greater increase in mindfulness compared to the low-usage subgroup after MMT. (v) The high-usage subgroup will exhibit a greater increase in subjective vitality compared to the low-usage subgroup after MMT.

The fourth objective of this study is to examine whether mindfulness and subjective vitality mediate the relationship between MMT and burnout or work engagement. The results of this study are predicted as follows: (i) Mindfulness will mediate the relationship between MMT and burnout. (ii) Mindfulness will mediate the relationship between MMT and work engagement. (iii) Subjective vitality will mediate the relationship between MMT and burnout. (iv) Subjective vitality will mediate the relationship between MMT and work engagement.

## Methods

2

### Trial design

2.1

This study is a two-arm randomized controlled trial that will investigate the effects of MMT on stress, burnout, and work engagement of office workers. Office workers aged 19 years or older who complain of job-related stress will be recruited for this study. Participants will be randomly allocated to either the experimental or control group. Participants will take part in the study for 8 weeks. The intervention will be conducted over 4 weeks. Outcome variables will be assessed at baseline (T1), post-intervention (fourth week; T2), and at follow-up (eighth week; T3).

This trial was registered with the Clinical Research Information Service (CRIS), Republic of Korea (KCT0009458). This trial adheres to the SPIRIT guidelines and is conducted following the tenets of the Declaration of Helsinki. Figure 1 describes the flow chart of this trial design.

**Figure 1 fig1:**
[figure not shown]
Study flow chart. MMT, mobile mindfulness training.

### Study setting

2.2

This trial will be conducted in companies and institutions in the Republic of Korea with the approval of the Institutional Review Board of Kyung Hee University. Participants will be recruited through advertisements displayed in their workplaces. People interested in participating will be gathered at a location within their workplace and informed about the study. After receiving written informed consent, they will be screened to assess the inclusion and exclusion criteria. The intervention will be smartphone-based.

### Eligibility criteria

2.3

#### Inclusion criteria

2.3.1

Office worker over 19 years of age.Participants subjectively complaining of stress related to various issues at work.Participants who can participate in the study for 8 weeks.

#### Exclusion criteria

2.3.2

Participants unable to use the application.

### Interventions

2.4

#### Mobile mindfulness training (MMT)

2.4.1

The experimental group will be provided with a mobile application called InMind for the first 4 weeks. InMind is a mental health management application developed by Demand Inc. and serviced in Korea and Japan. InMind provides mindfulness-based meditation, healing sound, and ACT-based contents (e.g., emotional diary, restructuring) for mental health, but this study used only meditation and healing sound as components of the intervention. InMind provides guided meditation, which consists of a two-week meditation curriculum for regular training and event-specific meditation for coping with specific situations. Guided meditation includes a variety of meditations such as breathing meditation, body scan, yoga, eating meditation, walking meditation, and loving-kindness meditation. Furthermore, it provides nature-based healing sounds that can help with relaxation and mindfulness.

Participants will be asked to follow both daily and event guidelines while using InMind for 4 weeks (Table 1). For the daily guidelines, participants will be asked to perform a two-week meditation curriculum consisting of 14 sessions, with participants being expected to perform one session per day. This curriculum consists of mindfulness-based training such as sitting meditation, body scan, yoga, eating meditation, and walking meditation. Each session is provided as an audio recording and is approximately 10 min long. Participants will be asked to perform the curriculum twice during the four-week intervention period.

**Table 1 tab1:** Guideline for mobile mindfulness training.

No.	Guideline	
	Event	Daily
1	In acute stress situations, select and perform one or more of the following: Concentrative meditation for quick relaxation Healing sound for relaxation.	Perform a “Two-week meditation curriculum,” one session per day. Repeat a total of 2 times for 4 weeks. *(Two-week meditation curriculum)* Session 1. Program introduction (4 min) Session 2. I want to have a deep sleep (9 min) Session 3. Breathe with nature (10 min) Session 4. Come back to breathing at any time (13 min) Session 5. Focus on the object and relax (11 min) Session 6. My happy moment (11 min) Session 7. Focus on posture and breathing (11 min) Session 8. Time to look at my mind (10 min) Session 9. Breathe comfortably and focus on your senses (12 min) Session 10. Mindfulness yoga (13 min) Session 11. Eating meditation (10 min) Session 12. Walking meditation (10 min) Session 13. Compassion meditation (13 min) Session 14. Program closure (11 min)
2	In chronic stress situations, select and perform one or more of the following: Mindfulness meditation for emotional regulation Healing sound for emotional regulation.	
3	In interpersonal stress situations, select and perform one or more of the following: Compassion meditation for improving positive emotion Healing sound for improving interpersonal relationships.	
4	In daily life stress situations, select and perform one or more of the following: Meditation that is easy to apply in daily life (e.g., meditation for deep sleep, morning meditation for a special day) Healing sound	

For event guidelines, whenever participants experience stress during their daily or work life, they will be asked to practice meditation or listen to healing sounds recommended for that stressful situation. A total of four types of stressful situations are listed, namely, acute work stress, chronic work stress, interpersonal stress, and daily life stress. In acute-stress situations, concentrative meditation and healing sounds will be recommended for quick relaxation. In chronic stress situations, mindfulness meditation and healing sounds will be recommended for emotional regulation. In situations of interpersonal stress, compassion meditation and healing sounds will be recommended to improve interpersonal relationships. In situations of daily life stress, meditation that is easy to apply in daily life (e.g., meditation for deep sleep, morning meditation for a special day) and healing sounds will be recommended. Participants will be asked to autonomously perform the recommended content for the relevant stressful situation. Education on daily and event guidelines will be provided to improve compliance with the intervention protocol.

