### Statistical analyses

2.13

Analyses will be conducted according to the Intention-To-Treat (ITT) principle, and missing data will be imputed using the expectation maximization algorithm.

First, to investigate the effectiveness of MMT, a 2 (group: experimental vs. control) × 2 (survey time: T1 vs. T2) repeated-measures ANOVA will be performed for MBI-GS, UWES, PSS, CMAS-R, and IVS. If the interaction between the group and survey time is significant, a simple main effect analysis will be performed. Second, a paired *t-*test will be performed on MBI-GS, UWES, PSS, CMAS-R, and IVS in the experimental group to examine the follow-up effect of MMT. Third, a subgroup analysis will be performed to investigate the difference in effectiveness depending on the amount of application usage. For this purpose, 2 (subgroup: high-usage vs. low-usage) × 2 (survey time: baseline vs. post-intervention) repeated-measures ANOVA will be performed. Data from both the experimental and control groups will be used for subgroup analysis. If the interaction between the subgroup and survey time is significant, a simple main effect analysis will be performed. Fourth, a mediating effect analysis will be performed to investigate whether mindfulness and subjective vitality mediate the relationship between application use and burnout or work engagement.

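### App use is partly triggered by stress, so the high- versus low-usage comparison in the third objective is confounded by need, in a direction that cannot be told in advance

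*Protocol article*

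**What the plan says.** The intervention in section 2.4.1 has two parts. The daily part is a fixed assignment of 14 sessions; Table 1 reads "Perform a “Two-week meditation curriculum,” one session per day. Repeat a total of 2 times for 4 weeks". The event part has no fixed amount: "whenever participants experience stress during their daily or work life, they will be asked to practice meditation or listen to healing sounds", and "Participants will be asked to autonomously perform the recommended content for the relevant stressful situation". Under Table 1, an event can be answered with a healing sound alone.

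The third objective (Introduction) makes five predictions of the form "The high-usage subgroup will exhibit a greater reduction in burnout compared to the low-usage subgroup after MMT". One of them concerns perceived stress. Section 2.13 states that "a subgroup analysis will be performed to investigate the difference in effectiveness depending on the amount of application usage", by means of a "2 (subgroup: high-usage vs. low-usage) × 2 (survey time: baseline vs. post-intervention) repeated-measures ANOVA will be performed". It adds that "Data from both the experimental and control groups will be used for subgroup analysis". The article does not separate daily from event use in this analysis and names no covariate. The Discussion expects effectiveness to grow with usage and counts this comparison among the study's main implications.

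**The concern.** The two sources of usage mean different things. The daily curriculum is the same request for everyone, so the number of sessions completed mainly measures adherence. Event use is requested in proportion to stress. Two equally compliant participants will log different amounts if one has a harder month than the other.

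A split on amount of usage therefore sorts people partly by their stress. Perceived stress is an outcome of the comparison, and burnout and engagement are plausibly related to it. The planned ANOVA would attribute to the app a difference in change that may come from who needed it. This could hide or reverse a real relation between use and benefit, or create one where none exists. The third objective, with its five hypotheses, could not then be read as dose-response.

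Section 2.13 also names application use as the exposure in the mediation analysis. If that means amount of use, the same problem reaches the fourth objective.

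**Working it through.** **The plan's own figure.** The article gives no figure for the usage comparison. Its sample size (section 2.6) reproduces. With f = 0.15, two-sided α = 0.05, two groups, two measurements and an assumed correlation of 0.5, power is 0.804 at N = 90 and 0.795 at N = 88. Then 45/(1 − 0.20) = 56.25, rounded up to 57 per group, or 114 in total. The present point does not touch that calculation. The minimum of 45 per group is borrowed below as a subgroup size.

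**Model (all inputs assumed).** Score at start: T1 = S + E. Score at end: T2 = S + D + N. Here S is stable stress (variance 0.5), E a transient peak at the start (0.5), D stress arising in the period (0.3) and N noise (0.2). Baseline SD is 1. Usage is adherence (variance 1) plus b times one or more standardised stress components, and U is usage rescaled to SD 1. For a median split,

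high-minus-low difference in change = 2√(2/π) × cov(change, U) = 1.596 × cov(change, U).

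Negative values mean that high users improve more.

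**No true dose effect:**

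| What drives event use | cov(change, U) | Difference (SD) |
|---|---|---|
| Nothing stress-related | 0 | 0.00 |
| Stable stress, b = 0.5 | 0 (S cancels in the change) | 0.00 |
| In-period stress, b = 0.5 | 0.5 × √0.3 / √1.25 = 0.245 | +0.39 |
| In-period stress, b = 1 | √0.3 / √2 = 0.387 | +0.62 |
| Baseline peak, b = 0.5 | −0.5 × √0.5 / √1.25 = −0.316 | −0.50 |
| Baseline peak, b = 1 | −√0.5 / √2 = −0.500 | −0.80 |
| All three, b = 0.5 | (0.274 − 0.354) / √1.75 = −0.060 | −0.10 |

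Simulation with 2,000,000 draws per row agrees with the closed form. With 45 per subgroup, the chance of a significant result in the wrong direction is 46% and 86% in the two in-period rows. The chance of a significant but false greater reduction is 68% and 98% in the two baseline-peak rows.

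**True dose effect of 0.2 SD per SD of usage.** The unconfounded difference is 1.596 × (−0.2) = −0.32. In-period stress moves it to +0.07 (b = 0.5) or +0.30 (b = 1). A baseline peak moves it to −0.82 or −1.12.

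**What baseline adjustment does.** Since var(T1) = 1 and cov(T1, T2) = 0.5, the covariance left after adjusting for T1 is cov(T2, U) − 0.5 × cov(T1, U). Values for b = 0.5:
- Baseline peak: 0 − 0.5 × 0.316 = −0.158, half of the unadjusted −0.316.
- Use that follows the observed starting score (S and E equally): 0, because cov(T2, U) is then half of cov(T1, U).
- In-period stress: 0.245, unchanged.
- Stable stress only: 0.316 − 0.158 = +0.158, where the unadjusted change had none.

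Adjustment helps with differences visible at the start. It does not make the contrast causal.

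**The case against.** Four arguments deserve weight.

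1. *A reader might infer that the comparison is biased against its own hypotheses.* The event rule suggests this, because people with a bad month use the app more and also finish worse. The document does not support that as a conclusion. Section 2.3.1 admits people who complain of work stress, so a temporary peak at entry is plausible. If such a peak drives use, regression to the mean favours the hypotheses. This objection stands, and no direction is claimed here.

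2. *The definition of usage may be in the fuller protocol or SAP.* The article gives no metric or cut-off, and that gap is not the point. It also does not say that usage means total use; that would be a reader's inference. But a metric or cut-off supplied later would not remove the problem unless it separated event from curriculum use. The event instruction, the usage split and the named ANOVA are all in the text.

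3. *Any large magnitude is assumed.* This stands. In another illustration, each SD of use lowers change by 0.30 SD and each SD of in-period stress raises it by 0.50 SD. If event use makes up 30% of usage variance and correlates 0.32 with stress, the difference is 1.596 × (−0.30 + 0.50 × √0.3 × 0.32) = −0.34, against −0.48 without stress-driven use. About 70% survives and nothing reverses. Only the more extreme inputs (50%, 0.71) bring it to −0.08.

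4. *Removing event use changes the question, and curriculum completion is not clean either.* Event practice is part of the intervention, and stressed workers may skip assigned sessions. Both stand. They are reasons to keep overall usage as a second split and to make only a modest claim.

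**Conclusion.** The point holds in limited form. The event instruction makes part of app use a response to stress, and the planned unadjusted subgroup × time ANOVA includes stress among its outcomes. The high/low contrast is therefore confounded by need. The bias runs against the hypotheses if stress arising in the period drives use, in their favour if a transient baseline peak does, and is near nil if stress is stable. The article offers nothing that fixes the net direction or size. The illustrative shifts, from −0.80 to +0.62 SD with no true effect, depend on the assumed variance shares and coefficients.

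The damage is confined to the third objective and, if its exposure is amount of use, the mediation analysis. The randomised T1–T2 comparison and the sample size are unaffected. Since recruitment has not started (section 3.1), the change should be made now.

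**What to change.** In section 2.13, with matching words in the third objective:

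- Define the main usage split by completed assigned curriculum sessions. Since "Participants will be asked to perform the curriculum twice during the four-week intervention period" and the curriculum has 14 sessions, the count runs from 0 to 2 × 14 = 28.
- Report event meditation and healing-sound use separately. Keep overall usage as a secondary or sensitivity split.
- Adjust the comparison for the outcome and PSS at the start of each participant's app period: T1 in the experimental group and T2 in the wait-list group. Both are already collected.
- Call the result a non-randomised, exploratory association, and remove the dose-response reading from the Discussion.

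The cost is a few sentences and no new data collection, provided the app log separates curriculum sessions from other content. The main split would then speak to the assigned sessions and not to all use. Confounding by in-period stress and by self-selected adherence would remain, and baseline adjustment only partly deals with a transient starting peak. The label of association is therefore needed whichever split is used.
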